To determine the extent to which providers utilize the Beehive platform to deliver measurement-based care (Aim 2), we adopt two different approaches. First, we will examine whether a service user’s treatment team lead reviews completed surveys in Beehive, which is recorded by the application. During service user registration in Beehive, EP providers designate the service user’s treatment team lead, typically their primary clinician. Once a survey respondent completes a survey in Beehive, the data are immediately available to view in the Beehive dashboard. The Beehive survey reports will include a variable that shows whether or not each survey has been viewed by the service user’s treatment team lead (binary yes/no). Research staff will use this data to determine the degree to which providers are actively viewing data collected in Beehive.

To explore how Beehive data are used by those who frequently utilize the application, two types of in-app queries were developed: urgent clinical issues and data-use questions. Urgent clinical issues are a type of notification (in-app and email) in Beehive that encourages EP staff to review service user data. These notifications trigger if, during registration or survey completion, a service user endorses risk-to-self or risk-to-others on the Modified Colorado Symptom Index (MCSI) [26], the intent to stop taking their medication [27], or lack of a permanent address. Beehive displays urgent clinical issues on a dashboard widget and to resolve them, users must indicate how they used the data in care. Additionally, an in-app query is presented to the service user’s treatment team lead every ten visits to the service user’s data page. Data-use questions assess (1) if the data was reviewed during a session with the service user or support persons and, if yes, (2) how the data was used as part of care.

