A key operationalization of the exposure indicator will be based on a composite indicator for any review of the service users’ completed surveys. In particular, this variable will be scored a 1 for a given service user in a given follow-up assessment if the treatment team lead reviewed the service users’ completed survey data. The comparison groups are defined by clinician metrics from Beehive aggregated over the 6-, 12- and 18-month assessment period, and the primary analysis is based on a composite indicator for any review of the service users’ survey data by the treatment team lead. We will also assess timepoint-specific changes in psychotic symptom severity for each of the half-yearly assessment timepoints during the first 24 months, with the primary analysis based on a time-varying indicator for any endorsement of “impact on treatment plan” on the in-app queries as a time-varying independent variable.

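### Aim 3 names two primary exposures without a hierarchy, and the query-based one scores periods in which nobody was asked the same as periods in which the answer was no

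*Protocol article*

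**What the plan says.** In the protocol article, Data analysis, the paragraph defining the Aim 3 exposure says that "the primary analysis is based on a composite indicator for any review of the service users’ survey data by the treatment team lead". The next sentence adds an analysis of change in psychotic symptom severity at each six-monthly assessment up to 24 months. Its exposure is worded as follows: "with the primary analysis based on a time-varying indicator for any endorsement of" an impact on the treatment plan in the in-app queries. Both exposures carry the word primary, and neither is ranked above the other.

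The queries are described under Outcome measures and instruments. Their purpose is given first: "To explore how Beehive data are used by those who frequently utilize the application, two types of in-app queries were developed". The two types are urgent clinical issues and data-use questions.

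- A data-use question is put to the "treatment team lead every ten visits to the service" user's data page. It asks whether the data were reviewed in a session and, if so, how they were used.
- An urgent clinical issue is raised when the service user endorses risk to self or others on the MCSI, an intention to stop medication, or having no permanent address. Of these issues the article says that "to resolve them, users must indicate how they used the data in care".

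The MCSI is listed among the Aim 3 outcomes. The missing-data section provides multiple imputation for follow-up and change scores only.

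**The concern.** An indicator of any endorsement can equal 1 only where a question was put. In a period with no query it is 0 whatever the clinician did with the data. A team lead who opened a page nine times and used the data each time is scored like one who was asked and said no. The comparison group then mixes two different states, in proportions set by page traffic, while the article itself describes the queries as a tool for studying frequent users.

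There are two further consequences. With two exposures called primary under one aim, either could be reported as the Aim 3 result. And if answers given to close an urgent issue feed the indicator, part of the exposure is switched on by items inside the MCSI, which is itself an outcome.

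**Working it through.** The article gives no visit rate, alert rate, endorsement rate, power or effect size for Aim 3, so there is no figure of its own to reproduce. Only two inputs come from the documents: the ten-visit trigger, and six-monthly assessment over 24 months (four windows). The rest is assumed.

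**1. How often is the data-use query absent?** Let visits to one service user's page in a six-month window be X ~ Poisson(m). In the first window a query fires if X ≥ 10. With a running counter, a window that starts with r visits since the last query fires if X ≥ 10 − r, and the next window starts with (r + X) mod 10. Averaging over r gives:

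| Mean visits m | Query fires, windows 1 to 4 (%) | Average (%) | Absent (%) |
|---|---|---|---|
| 4 | 0.8, 27.5, 49.5, 36.6 | 28.6 | 71.4 |
| 8 | 28.3, 80.7, 76.6, 75.5 | 65.3 | 34.7 |
| 10 | 54.2, 86.3, 87.5, 87.5 | 78.9 | 21.1 |
| 20 | 99.5, 99.9, 99.9, 99.9 | 99.8 | 0.2 |

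If the counter restarts each window, the share without a query is P(X < 10): 97% at mean 5, 46% at mean 10 and 0.5% at mean 20. With over-dispersed visits (negative binomial, k = 1) it is 84%, 61% and 39%.

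These shares concern the data-use query alone. They equal the share of windows that can only be 0 if urgent-issue responses do not feed the indicator. If such responses do count, the share is lower.

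**2. What share of the zeros were never asked?** Assume 30% endorsement when asked and data-use queries only.

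- Mean 4: 71 / (71 + 0.7 × 29) = 71 / 91.3 = 78%.
- Mean 8: 35 / (35 + 0.7 × 65) = 35 / 80.5 = 43%.

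**3. What if urgent-issue responses count and the outcome is the MCSI?** This was simulated with no true effect in 400,000 records. Assumptions: MCSI SD 11, baseline-to-follow-up correlation 0.4 or 0.6, alerts in 10% or 25% of records, endorsement probability 0.3 or 0.6 per query, Poisson mean of 5 visits with the counter restarting. The entries are exposed minus unexposed change in MCSI points; a positive value means that the exposed look worse.

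| Alerts arise from | Unadjusted | Adjusted for baseline MCSI |
|---|---|---|
| nothing related to the MCSI | −0.04 to +0.05 | −0.07 to +0.06 |
| the follow-up MCSI | +3.8 to +6.7 | +6.2 to +9.4 |
| the baseline MCSI | −6.7 to −3.9 | −0.12 to +0.05 |

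The second and third rows are extremes in which every alert comes from the MCSI. Medication and housing alerts would dilute them. The first row shows that coding unasked periods as 0 misclassifies exposure but creates no spurious difference by itself.

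**The case against.** The strongest reply is that an article condenses a fuller plan, and the coding of a derived exposure is usually settled there. No sentence says that an unqueried window is scored 0. That stands as far as an explicit rule goes. But the article does fix the form of the indicator, and any endorsement, taken as written, gives 0 where no question was shown.

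The two primary labels can be read as one per analysis: the second is introduced as an additional, timepoint-specific analysis, and the Aim 2 text foresees primary and alternative forms of the usage metrics. That reading is possible. Both analyses still serve Aim 3, and nothing ranks them.

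Three stronger readings are tempting but not supported.

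- A reader might infer that a positive answer is driven by the MCSI. MCSI risk items are one of several alert triggers, and the ten-visit question has no MCSI trigger. No passage says that closing an urgent issue counts as a treatment-plan impact. The Aim 2 text in Data analysis speaks of queries presented periodically, which fits the ten-visit question better.
- A reader might infer that the indicator is all but forced to 1 after an alert. Stating how data were used is not the same as reporting a changed treatment plan, and the response options are not given.
- A reader might infer that the zeros are mostly people never asked. That depends on traffic: under the assumptions above it is 78% at a mean of 4 visits but 43% at 8.

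The outcome of the second analysis is also named only as psychotic symptom severity, with no instrument. The MCSI is a plausible reading, but Table 1 also lists clinician-rated symptom scales.

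**Conclusion.** The point holds in limited form. Two Aim 3 exposures are called primary with no order between them, and the query-based one does not separate 'not asked' from 'asked, no'. Its size depends on page traffic, which the documents do not report: under Poisson visits and a running counter, the data-use query is missing from about 71% of windows at a mean of 4 visits and from under 1% at a mean of 20. The problem therefore runs from dominant to negligible, although over-dispersed visits would keep it substantial even at high averages. The certain harm is misclassified exposure. Bias linked to the outcome is conditional: it needs urgent-issue responses to count and the outcome to be the MCSI, and its direction then depends on whether the alert arises at baseline or at follow-up.

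**What to change.** Change the wording of the Aim 3 analysis before data are analysed:

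1. Make review by the treatment team lead the single primary exposure and label the query indicator secondary.
2. Code 'not asked' as its own level, and compare 'asked, yes' with 'asked, no' among periods with at least one data-use query.
3. State which query responses count as an impact on the treatment plan.
4. Leave urgent-issue resolutions out of the exposure and report them descriptively.

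No new data collection is needed. The cost is that the query contrast rests on fewer periods and has a wider interval. It also applies only to service users whose pages are visited often, and the report should say so.

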#### Analysis of population and missing data

All EP program service users are eligible to participate in the study and complete surveys on Beehive. To address attrition in longitudinal survey completion and missing data, we will use multiple imputation to impute follow-up assessment scores and change scores based on them, as appropriate.

#### Qualitative analyses

Though qualitative data is not be directly linked to Beehive user IDs, we also use interview data to examine service user-, provider- and program-level barriers and facilitators to enrollment and completion via semi-structured qualitative interviews with service users and providers. Service user-, provider- and program-level implementation barriers will be identified utilizing an inductive approach to thematic analysis. Purposive sampling will be used to recruit participants of service users and providers across clinics where Beehive adoption and implementation has been both high and low, and with service users who have and have not received measurement-based care. Multiple coding will be adopted, and where possible, service users and providers will be involved in developing the topic guide and reviewing the data analysis and interpretation.

### Data monitoring

Research staff monitor the enrollment of eligible participants on a weekly basis and discuss progress with EP programs at regular meetings to facilitate enrollment of all potential participants. Our internal data management team monitor data as it is collected by sites in Beehive, such as service user enrollment and completion of the MCSI, to ensure data quality. We also periodically monitor datasets exported from Beehive for statistical analyses, including evaluating individual survey data, for missing or incomplete data. We provide feedback to sites, such as following up about missing diagnoses, if applicable. We conduct an ongoing analysis of the enrollment of service users and support persons solely to ensure that the study is appropriately reaching the target population.

#### Formal committee

In addition to our study team that performs regular monitoring of study data, we have also established an Executive Committee meeting that meets annually to review study progress and interim analysis results. The Executive Committee consists of the principal investigator, co-investigators, and key consultants.

#### Interim analysis

Formal interim analyses are not needed to assess the trial intervention on an experimental group as all eligible service users are eligible to participate in the study.

## Ethics and dissemination

### Research ethics approval

The institutional review board of the University of California, Davis, approved the study (1403828-21, California Collaborative Network to Promote Data-Driven Care and Improve Outcomes in Early Psychosis [CORE]). Additionally, several of the counties and universities with a program participating in EPI-CAL required a separate review and approval of the project by their institutional review board or compliance department.

Some EP programs require approval by additional oversight bodies associated with California counties, universities, and/or community-based organizations. These oversight bodies review and approve research prior to initiation of any research activity the EP programs they oversee.

### Protocol amendments

Any modifications to the protocol that materially impact the study are reviewed and approved by UC Davis IRB before implementation. If there are significant changes to the study plan, such an amendment will be agreed upon by the project’s sponsors including the NIMH, the MHSOAC, the California county sponsors, and One Mind. All changes to the protocol, forms, and study documentation are first approved by UCD IRB before being presented to the other oversight bodies that are involved in this project.

### Consent or assent

Written consent is obtained from study participants for the following study-related components: focus groups, feedback interviews, fidelity assessments, and surveys completed by service users, support persons, and EP program staff. Assent is obtained for minors, with their legal guardian signing the consent on their behalf. Asynchronous written consent in English and Spanish will be obtained for cognitive testing. If a participant does not speak English and we have the language capacity on our internal team to conduct the informed consent process, the consent and/or assent forms is translated into the participants’ preferred language by UC Davis Medical Interpretive Services and the consent is conducted in that language. We follow standard informed consent practices and EPI-CAL research staff will be responsible for administering the consent and ensuring all documentation is completed. Every research staff member is required to complete all required HIPAA and CITI training, certificates of which are kept on file for all personnel, prior to engaging in human subjects research activities.

### Ancillary studies

Data collected for this research may also be used for future research studies, which is described in the EULA that participants complete when they make decisions about sharing their data for research. We do not share any personally identifiable information. Our goal is to make more research possible. These studies may be done by researchers at this institution or other institutions. Data may be placed in one or more external scientific databases for access and use. We will not ask participants for additional permission to share de-identified information. Efforts are be made to limit the use or disclosure of participant personal information to people who need to review this information.

### Confidentiality

Data is primarily stored at UC Davis; some data are also be stored at UCSF and UCSD with similar protections outlined below. All information collected does not include any names or references to individual service users, support persons, or staff or personal health information. The only PHI that the research team has access to from Beehive data is the service user’s zip code, month and year of birth, and dates of service. No health records or identifiable information should be shared with our team, except to facilitate staff interviews. The study investigators and primary research team are the only ones who will have access to the data. We regularly release data to the ENDCC with the following stipulations: (a) dataset only includes service users who have given their permission for us to share it with ENDCC, (b) dataset does not include any identifiers or free-text fields, (c) dataset does not include the study ID assigned to the service user in Beehive. For the electronic files and datasets, copies of each file will be maintained on HIPAA-compliant cloud storage, e.g., UC Davis’s OneDrive. All copies of these electronic files are also encrypted. Data will be stored for after the end of the project to allow ongoing data analysis and publication. All oversight of data sharing will be provided by the project manager and the Principal Investigator [name]. E-mailing of files is only allowed if data is de-identified and can be sent via encrypted, password-protected messaging.

### Dissemination

#### Dissemination plan

Our team plans to disseminate the results of this project in a variety of ways. Results and information from the clinical trial are submitted to ClinicalTrials.gov as outlined in the policy and according to the specific timelines stated in the policy (identifier NCT04007510; registered 07/05/2019). Results of the study will also be published in peer-reviewed academic journals or presented at conferences to share our findings with the larger community. Products from this project (e.g., webinars, written products, presentations) are available on the EPI-CAL website (https://epical.ucdavis.edu/). Results of the evaluation will also be communicated with our EP program partners via biannual advisory committee meetings, deliverables, annual reports, or larger presentations based on the needs of our partners.

#### Publication policy

We established an EPI-CAL Publications Committee and corresponding publication guidelines to ensure that (1) the rich data derived from EPI-CAL are used to their full productivity, (2) publications are not iterative, and each publication makes the best use of the full data set, (3) project resources are used wisely, (4) researchers’ intellectual ideas are respected. Authorship for publications derived from EPI-CAL data is determined following the International Committee of Medical Journal Editors guidelines. There is no intention for the use of professional writers on authorship of work derived from project data.

## Discussion

The goal of the current study is to assess the feasibility of establishing a Learning Health Care Network of EP clinics in California that implement harmonized data collection using a custom-built application, Beehive. EPI-CAL’s LHCN aims to improve coordination and increase knowledge sharing across heterogenous EP programs, including university- and community-based CSC programs. Prior to implementation of the EPI-CAL LHCN, there has not been a unified attempt to harmonize core data metrics and outcome measures across the disparate EP programs in California. The core battery of evidence-based measures utilized in EPI-CAL’s LHCN focuses on treatment outcomes of importance to service users, providers, and support persons as the survey battery was designed with extensive input from those community partners.

The harmonized core data metrics collected across California EP programs are collected using a unique data collection and visualization application, Beehive. EP program providers will need sufficient training and support to implement a new method of data collection into their clinical practice, especially given the already high workloads and reporting requirements EP programs face. Our approach to a successful implementation of measurement-based EP care includes detailed training, ongoing access to training and resource materials, and consistent support via EPI-CAL team members. We conduct barriers and facilitator interviews to evaluate the effectiveness of the implementation process and refine our approach accordingly.

While collecting a harmonized dataset of key outcome measures is a major goal of EPI-CAL LHCN, the heterogeneity across programs enables detailed analysis of specific program elements that lead to program success and improved treatment outcomes for service users within the network. Specific program elements will be evaluated by conducting a fidelity assessment with each program. In addition to program elements, we will also examine if treatment outcomes vary based on clinician’s use of data in care. For example, we will examine treatment outcome differences across service users whose treatment team lead examines the service user-level data available in Beehive and whether they incorporate this data into care decisions. We will include relevant clinician metrics in our analyses of treatment outcomes, which include clinician demographic information collected at registration, such as degree level, and years working with this specific population.

Beyond establishing the California Learning Health Care Network of EP programs, EPI-CAL will provide a harmonized dataset to the EPINET initiative for the purpose of advancing early psychosis care, improving recovery outcomes, and scientific discovery. The contribution of outcomes data from the California network to the national level via EPINET will improve the development of EP care, early intervention, and provide even greater opportunities for large-scale evaluation and research of EP care.

## Data Availability

No datasets were generated or analysed during the current study.

## Abbreviations

ABCD: Adolescent brain cognitive development
AWS: Amazon web services
BARS: Brief adherence rating scale
BPRS: Brief psychiatric rating scale
CAB: Core assessment battery
CATS: Child and adolescent trauma screen
CHR: Clinical high risk
CITI: Collaborative institutional training initiative
COMPASS-10: Computerized prescriber support system- 10 item
CSC: Coordinated specialty care
DAQCORD: Data acquisition, quality and curation for observational research designs
DSM-5: Diagnostic and statistical manual of mental disorders, fifth edition
ENDCC: EPINET national data coordinating center
EP: Early psychosis
EPI-CAL: Early psychosis intervention network of California
EPINET: Early psychosis intervention network
EULA: End user license agreement
FEP: First episode of psychosis
FEPS-FS: First episode psychosis services fidelity scale
GASS: Glasgow antipsychotic side-effect scale
GF: R: Global functioning: Role
GF: S: Global functioning: Social
HIPAA: Health insurance portability and accountability act
INN: Innovations
IRB: Institutional review board
LEC: Life events checklist
LHCN: Learning health care network
MBC: Measurement-based care
MCSI: Modified colorado symptom index
MHBG: Mental health block grant
MHSA: Mental health services act
MHSOAC: Mental health services oversight and accountability commission
MIRECC GAF: Mental illness research, education, and clinical center global assessment of functioning
NIMH: National institute of mental health
PANSS-6: Positive and negative symptoms of schizophrenia scale − 6 item
PCL-5: PTSD checklist for DSM-5
PEI: Prevention and early intervention
PHI: Protected health information
PL-CAB: Program level core assessment battery
PSP: Primary support person
PTSD: Post traumatic stress disorder
PWI: Personal wellbeing index
QPR: Questionnaire about the process of recovery
SCORE-15: Systemic clinical outcome and routine evaluation − 15 item
SDM-Q-9: Shared decision making questionnaire − 9 item
UCD: University of California, Davis
UCSD: University of California, San Diego
UCSF: University of California, San Francisco
